### Sample size calculation

2.6

To achieve a two-tailed size effect (Cohen’s *d*) of 0.5 with 95% power, using the total PANSS scores and balanced observations in the two groups, the estimated size is 210 in total. Considering 20% of loss to follow-up, we aim to include a total of 252 patients in the study.

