Therefore, the primary objective of this prospective clinical trial is (1) to evaluate the efficacy of P-MCT compared to classical MCT in individuals diagnosed with psychosis, focusing on improvements in positive symptoms (especially delusions), insight, self-esteem, and treatment adherence. Moreover, some specific objectives of this trial include: (2) to validate the ML-based predictive model’s capacity to anticipate MCT treatment response, (3) to evaluate patient satisfaction with P-MCT comparing to classical MCT, integrating both quantitative measures and qualitative insights from focus groups, and (4) to refine the platform’s predictive algorithm through integration of treatment outcome data.

Given that P-MCT has not been previously evaluated and that the ML platform is a novel tool, hypotheses 2–4 are considered exploratory. Our hypotheses are as follows:

H1 - Primary (Comparative efficacy): P-MCT will yield comparable or superior improvements than classical MCT in outcome variables measuring treatment efficacy (positive symptoms, insight, self-esteem, and treatment adherence).H2 - Exploratory (Platform validation): The ML-based predictive model will demonstrate significant predictive capacity to anticipate post-treatment response to MCT on positive symptoms (especially delusions), insight, self-esteem, and treatment adherence, as assessed by the AUC (Area Under the Curve).H3 - Exploratory (Patient satisfaction): Patient satisfaction with P-MCT will be comparable or greater than with classical MCT, as assessed through both quantitative measures and qualitative insights from focus groups.H4 - Exploratory (Platform improvement): The integration of multimodal comprehensive pre-post treatment data from the classical MCT group will refine the machine learning algorithm, resulting in improved predictive accuracy for future patient cohorts.

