#### Comparative efficacy (H1)

2.7.1

To assess the interventions’ efficacy, improvements in the proximal targets of MCT, as defined in recent meta-analyses and meta-reviews (11, 12), will be analyzed using statistical methods (43). These targets include global positive symptoms, including delusions, cognitive insight, self-esteem and treatment adherence. Regression models for repeated measures will be used for each proximal target, with the treatment group (P-MCT or classical MCT) included as a covariate for comparison. Additionally, mean differences between baseline and post-treatment scores in each group will be compared using Student’s t-tests, or Mann-Whitney tests if the assumption of normality is violated. Missing data will be handled using multiple imputation techniques. Subgroup analyses will be conducted based on sex, age, and baseline symptom severity. Sensitivity analyses will assess robustness of findings. ANCOVAs will explore whether responses differ across participant profiles (44), with treatment as the independent variable and composite participant profiles as a fixed factor. Covariates will include number of sessions attended, online vs. face-to-face delivery, and session frequency. Participant profiles will be identified using unsupervised ML techniques.

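### The sample size is set on total PANSS, which no hypothesis or analysis tests, while primary hypothesis H1 covers four or five other outcomes with no primary one named, so the stated 95% power is not the power of H1

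*Protocol article*

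**What the plan says.** Section 2.6 (Sample size calculation) plans for a Cohen's d of 0.5 at 95% power, describes this as a "two-tailed size effect", and gives the basis and the result: "using the total PANSS scores and balanced observations in the two groups, the estimated size is 210 in total". It then allows for dropout: "Considering 20% of loss to follow-up, we aim to include a total of 252 patients in the study". No alpha is given.

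The Introduction states the primary objective as comparing P-MCT with classical MCT, "focusing on improvements in positive symptoms (especially delusions), insight, self-esteem, and treatment adherence". H1 repeats those four outcomes and is the only hypothesis labelled primary; H2 to H4 are labelled exploratory.

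Section 2.7.1 (Comparative efficacy) describes the H1 analysis: "These targets include global positive symptoms, including delusions, cognitive insight, self-esteem and treatment adherence". Each target gets its own repeated-measures model, and a t-test or Mann-Whitney test of change from baseline to post-treatment is added. Section 2.7.2 counts five key variables, with delusions separate from positive symptoms and adherence expressed as treatment completion.

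Total PANSS appears only in section 2.6. In section 2.2, PANSS is used through single items for eligibility.

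**The concern.** A sample size justification has to refer to the comparison on which the trial will be judged. Here it refers to a score that adds negative and general symptoms to the positive ones and is never compared between arms. Insight, self-esteem and adherence do not lie on that scale at all.

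H1, for its part, has four or five outcomes of equal standing. The text does not say which is primary, or whether one, some or all must favour P-MCT. Post-treatment is named for the t-tests, but no time point is fixed for the repeated-measures models, although there is also a six-month assessment. A reader of the results could not tell what error rate and power lie behind a claim that H1 was met. The Discussion nevertheless describes the sample as large enough to detect overall group differences.

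**Working it through.** **Inputs (section 2.6).** d = 0.5; power 95%; two-sided; 1:1 allocation; 20% loss. Alpha is not stated; 0.05 is assumed and tested in step 1.

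**1. Reproducing 210.**
- Normal approximation: n per arm = 2(1.960 + 1.645)² / 0.5² = 104.0, so 104 per arm, 208 in total.
- Noncentral t: 104.93, so 105 per arm, 210 in total, with power 95.0%.
- One-sided at 0.05 (normal approximation): 87 per arm, 174 in total, which does not match.

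So 210 is one two-sided comparison of one continuous outcome at alpha 0.05. Because d is standardised, the result carries over to any single continuous outcome with a true d of 0.5. It does not carry over directly to adherence if that is analysed as binary completion.

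**2. After dropout.** 252 × 0.8 = 201.6 evaluable, about 101 per arm. Power for one test at 0.05 is 94.2%.

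**3. H1 as a whole.** The text gives no success rule, so two were computed.

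*Any one outcome suffices, each tested at 0.05.* For independent outcomes the chance of at least one false positive is 1 − 0.95^k: 1 − 0.95⁴ = 18.5% and 1 − 0.95⁵ = 22.6%. For correlated outcomes it was simulated with equicorrelated normal statistics.

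| Outcomes | Independent | Correlation 0.5 | Correlation 0.7 |
|---|---|---|---|
| 4 | 18.5% | 15.6% | 13.1% |
| 5 | 22.6% | 18.2% | 14.8% |

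*All outcomes must succeed, true d = 0.5 on each, 105 per arm.* Simulated power for correlation 0 to 0.7 is about 82% to 88% for four outcomes and 78% to 87% for five.

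**4. If four outcomes shared the 5%, d = 0.5 on each.**
- Bonferroni (0.05/4 = 0.0125), power per outcome: 86.4% with 210 evaluable, 84.7% with about 202. The matching unadjusted figures are 95.0% and 94.2%.
- Holm with about 202 evaluable, correlation 0 to 0.7 (simulated): about 91% to 93% average per outcome, 96% to 99.9% for at least one, and 79% to 85% for all four.

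**5. Whether d = 0.5 transfers.** The Introduction cites MCT effects of g = 0.47 (positive symptoms), 0.35 (insight) and 0.17 (self-esteem). Purely as illustration, if the difference between P-MCT and MCT equalled those values, power for a single test at 105 per arm would be about 92%, 71% and 23%. The article gives no estimate for this contrast, in which the arms differ only in homework.

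**The case against.** - **The calculation is not empty.** A reader might infer that the 95% applies to nothing the trial will test. The documents do not support that. The calculation uses a standardised effect, so it holds for any single continuous H1 outcome with a true d of 0.5, and naming one as primary leaves 210 unchanged at that d. This objection stands and limits the point.
- **The inflated error rate is conditional.** A reader might also infer that the trial runs an 18% to 23% false-positive risk. That needs the rule that any one outcome suffices, which the article never states. H1 can equally be read as requiring all four, in which case the cost is power.
- **An unseen analysis plan may settle multiplicity.** Testing order, adjustment and the relation of the t-tests to the repeated-measures models are commonly left to it. Their absence from an article is no finding. But an analysis plan cannot make section 2.6 agree with H1: one names total PANSS and the other does not.
- **The trial is called an exploratory proof of concept (section 2.1).** This softens the case for strict familywise control. It does not remove the mismatch, because the same sentence states a superiority aim and the Introduction reserves the exploratory label for H2 to H4.

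**Conclusion.** The point holds in a limited form. The sizing outcome is not an H1 outcome, nothing in the article reconciles the two, and H1 has no named primary outcome or success rule. The stated 95% is the power of one two-sided test of one continuous outcome at d = 0.5, with alpha 0.05 inferred from the reproduced 210. For H1 as a whole, power and error are undefined until a rule is given. With d = 0.5 on every outcome, requiring all to succeed gives about 78% to 88% power. Accepting any one gives about 13% to 23% overall false-positive risk, depending on the number of outcomes and their correlation (0 to 0.7). The finding rests on the mismatch and the missing primary outcome, not on the lack of a multiplicity method.

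**What to change.** Before unblinded outcome data are seen:

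- Name one H1 outcome at one time point as primary, tested at two-sided 5%. PANSS positive score at post-treatment is one candidate: positive symptoms come first in H1, and PANSS is already administered. The article itself ranks no outcome, so the choice is the sponsor's.
- Make the remaining H1 outcomes secondary, in a fixed order or with Holm adjustment, and say whether delusions count separately.
- Rewrite section 2.6 for the named outcome, state alpha and justify d for the contrast between P-MCT and MCT. At d = 0.5, 210 evaluable gives 95.0%, and 252 enrolled with 20% loss gives 94.2%.
- If all four stay co-primary, state the success rule and the power that belongs to it, using the figures in step 4 of the working. The 84.7% there is Bonferroni power for one outcome and should not be reported as the power under Holm.

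The cost is protocol and analysis plan wording and a registry update. The downside is fewer outcomes that can be claimed as primary.

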**Methods:**

PERMEPSY is an international study funded by ERAPerMed (JTC2022) involving five clinical partners (Spain, Chile, France, Germany, Poland) and one technological partner (Spain). The project involves a proof-of-concept clinical trial recruiting 51 participants from each center for a total of 255 adult participants with psychosis in a prospective study (Registration: NCT06603922, 19-09-2024). The trial will test the efficacy of a Machine Learning (ML)-derived platform at predicting clinical and functional outcomes from baseline scores and compare a personalized MCT (P-MCT) to a classical MCT based on the platform’s predictions.

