### Participants

2.2

The sample will consist of patients with a diagnosis of non-affective psychosis, according to DSM-5 criteria (40). Participants will be recruited from multiple clinical centers (associated to the following clinical partners: Fundació Sant Joan de Déu [FSJD], Universitätsklinikum Hamburg-Eppendorf [UKE], Hôpitaux Universitaires de Strasbourg [UHS], Centre Hospitalier Universitaire de Nice (CHU de Nice), Institute of Psychology, Polish Academy of Science [PAoS] and Universidad del Valparaíso [UV]), including both inpatient and outpatient services, with a minimum of 51 patients per center. Recruitment will occur in psychiatric hospitals and community mental health centers. To facilitate recruitment, clinicians at these sites will receive detailed information about the study’s inclusion and exclusion criteria through local meetings and internal communications. Additionally, announcements will be posted in the centers to raise awareness and encourage referrals during routine clinical care. Inclusion criteria are (1): A DSM-5 diagnosis of non-affective psychosis (2); presence of positive symptoms during the past year (represented by a Positive and Negative Syndrome Scale [PANSS (41)] score equal or over 3 on the items measuring Delusions, Suspiciousness, or Grandiosity); (3) aged between 18 and 65 years old; (4) stable clinical condition with no expected changes in medication (as confirmed by clinical services); (5) no severe cognitive deficits (global assessment and/or information from clinical services). Exclusion criteria are: (1) previous attendance in MCT groups within the past year; (2) neurological disorders, history of head trauma, or premorbid IQ below 70 (based on medical reports and/or other sources); (3) a score equal or over 6 on the Hostility and Suspiciousness items of the PANSS Positive subscale; (4) aggressive behavior (reported by clinical services); (5) high suicide risk (verified through the DIAMOND clinical interview). Patients who do not meet the inclusion criteria will not be enrolled in the study but will be offered alternative treatment options or MCT at later stages.

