Machine learning based technological solutions have the potential to enhance the identification of predictive variables for treatment response, thereby facilitating clinical decision-making. In the PERMEPSY study, a harmonized retrospective database was used to train a machine learning algorithm capable of predicting changes in key clinical and functional outcomes, such as positive symptoms, delusions, insight, self-esteem, between others. These predictions are generated based on composite patient profiles derived from pre-treatment data (39, 50). The platform thus supports clinicians to recognize objective problem areas, such as cognitive biases to address in the therapy. By combining the recognition of object problem areas from the ML algorithm with information about subjective concerns reported by patients, the MCT can be tailored to the individual needs. Beyond these clinical and cognitive predictors, this study also exploratorily examines whether blood biomarkers (inflammatory markers and SP transcription factors at selected sites) can contribute to refining predictive models of MCT response, offering preliminary insights into potential biological correlates of therapeutic change. Furthermore, incorporating a gender-sensitive approach in the early stages of treatment could further optimize outcomes. The development of the prototype platform and its implementation in clinical practice therefore represents a significant methodological advancement, enabling patient stratification based on data-driven insights and technology-assisted personalization (39).

While PERMEPSY constitutes an innovative initiative in applying personalized medicine principles to psychological interventions in psychosis, its implementation presents certain methodological challenges. The multicentric nature of the trial may introduce variability in MCT delivery, a factor that will be mitigated through a standardized training program, monthly supervision sessions, and staff mobility for trainers. Additionally, although the total sample size (*n* = 252) is sufficient to detect overall group differences, statistical power may be inadequate for conducting detailed subgroup analyses (e.g., by gender or comorbidities). To address this limitation, ML models prioritizing the most predictive variables will be employed, thereby reducing the risk of overfitting.

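### The 20% loss allowance is multiplied on (210 × 1.2 = 252) rather than divided out (210 / 0.8 = 262.5), and the printed recruitment target is 252 in some places and 255 in another

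*Protocol article*

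**What the plan says.** Section 2.6 opens with the design inputs: "To achieve a two-tailed size effect", set at a Cohen's d "of 0.5 with 95% power, using the total PANSS scores", with "balanced observations in the two groups". From these, "the estimated size is 210 in total". The next sentence adds the attrition allowance: "Considering 20% of loss to follow-up, we aim to include a total of 252 patients in the study". No significance level is given.

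The Discussion (section 3) relies on the same total: "although the total sample size (*n* = 252) is sufficient to detect overall group differences".

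The Methods paragraph of the abstract gives another total, "recruiting 51 participants from each center for a total of 255 adult participants with psychosis", after naming five clinical partners. Section 2.2 turns the per-center number into a floor, "including both inpatient and outpatient services, with a minimum of 51 patients per center", and lists six institutions linked to the clinical partners, two of them French (Strasbourg and Nice).

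**The concern.** There are two linked problems in the stated numbers.

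The first is the inflation step. Loss to follow-up is a proportion of the patients enrolled. To have 210 left after losing 20%, one divides 210 by 0.80. Adding 20% of the 210 gives a smaller number, and the enrolment, loss and power printed in section 2.6 then do not fit together.

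The second is the target itself. The article prints 252 in sections 2.6 and 3 and 255 in the abstract. The floor of 51 per center in section 2.2, taken over five centers, is already above 252. A later reader who compares achieved with planned recruitment, or fills in the planned sample size in a trial report, has two numbers to choose from and no sentence that links them.

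**Working it through.** **Inputs.** From section 2.6: d = 0.5, two-tailed, power 95%, equal groups, 210 before loss, 20% loss, 252 after. From the abstract: 51 per center, total 255. Assumed: alpha = 0.05, because none is stated.

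**Step 1. Reproduce 210.** The normal approximation gives n per arm = 2(1.960 + 1.645)² / 0.5² ≈ 104, or 208 in total. The exact two-sample t-test gives 104.93 per arm, so 105 per arm and 210 in total, an exact match. A one-sided 5% test would give 174, so two-sided 0.05 is the reading that fits.

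**Step 2. Reproduce 252.** 210 × 1.2 = 252, an exact match. 210 / (1 − 0.20) = 262.5, which does not give 252. The allowance was therefore multiplied on.

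**Step 3. What the stated loss leaves.** Evaluable = enrolled × 0.80; power is from the two-sided t-test at d = 0.5.

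| Enrolled | Evaluable at 20% loss | Power |
|---|---|---|
| 252 (sections 2.6 and 3) | 201.6 | 94.2% |
| 255 (abstract) | 204.0 | 94.5% |
| 263 | 210.4 | 95.0% |
| 264 (132 per arm) | 211.2 | 95.1% |

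The 252 row is 8.4 patients short of 210. Rounded down to 100 per arm, its power is 94.0%.

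**Step 4. Loss at which 210 is still kept.** From 252: 1 − 210/252 = 16.7%. From 255: 1 − 210/255 = 17.6%. Both lie below the 20% that section 2.6 allows for.

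**Step 5. Enrolment that keeps 210.** 263 is 11 more than 252 (4.4%) and 8 more than 255 (3.1%). With equal arms, 264 is 12 and 9 more.

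**Step 6. The two printed targets.** 255 − 252 = 3 patients, or 1.2% of 252. Since 252 / 5 = 50.4, rounding up to 51 per center gives 5 × 51 = 255. That would explain the abstract's figure, but the article does not say so.

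Steps 2, 4, 5 and 6 do not depend on alpha. Only the powers in step 3 do.

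**The case against.** The strongest reply is that little follows from the error. Power moves by 0.5 to 0.8 of a point in a trial that section 2.1 calls an exploratory proof of concept, and no design or analysis choice turns on it. That stands, and it sets the weight of the point.

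Three further arguments soften the consequence. Total PANSS, used for the calculation, is not among the H1 outcomes in sections 1 and 2.7.1, so the figure says little about power for H1. Section 2.6 does not say at which visit the 20% applies; if it means six months, more patients could be available post-treatment. And section 2.7.1 plans repeated-measures regression, which can be more precise than the unadjusted t-test. Purely as an assumption, a baseline–outcome correlation of 0.2 would give a variance factor of 1 − 0.2² = 0.96, and 202 / 0.96 ≈ 210. The documents give no correlation. These arguments show that the shortfall is small; they do not make 252 the right result of a 20% loss. Nor does the planned multiple imputation, which does not in general restore the information in lost outcomes.

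A reader might infer a third target of 306 by multiplying 51 by the six institutions in section 2.2. The article does not support this. The abstract counts five clinical partners and states 255 itself, sections 2.1 and 2.7.4 speak of five countries, and the ethics approvals in sections 2.4 and 4 number five, one of them French. The natural reading is that the two French hospitals share one quota, though section 2.2 does not say so.

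A reader might also infer that the trial is underpowered, or that nobody could tell when recruitment is complete. About 94% power for d = 0.5 does not support the first, and a gap of three patients that rounding may explain does not support the second.

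**Conclusion.** The point holds as a minor error in a stated figure. On the article's own inputs, 20% loss from 252 leaves about 202 evaluable patients, not 210, and power is 94.2% rather than 95%. With 255 enrolled it is 204 and 94.5%. Keeping 210 takes 263, or 264 for equal arms. The powers rest on an assumed two-sided alpha of 0.05, which reproduces 210 exactly, and on the unadjusted t-test; the attrition arithmetic rests on neither.

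Separately, two recruitment targets are printed, 252 and 255, and the floor of 51 in section 2.2 exceeds 252 over five centers. This is a discrepancy between statements that a condensed article cannot leave to a fuller document to resolve, but it amounts to three patients.

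**What to change.** State one target in the abstract and in sections 2.2, 2.6 and 3. The cheapest choice is 255, which already matches five centers of 51. Section 2.6 could then say that, with 20% loss, 255 enrolled patients leave 204 evaluable and give about 94% power for d = 0.5, and that 264 would be needed to keep 95%. State the alpha used. In section 2.2, add that the two French institutions count as one center for the quota, if that is intended.

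The cost is wording, plus a stated power about one point lower. No change to design or recruitment is needed unless the sponsor wishes to hold 95% at 20% loss, which would mean 9 more patients than 255.

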### Data analysis

2.7

#### Comparative efficacy (H1)

2.7.1

To assess the interventions’ efficacy, improvements in the proximal targets of MCT, as defined in recent meta-analyses and meta-reviews (11, 12), will be analyzed using statistical methods (43). These targets include global positive symptoms, including delusions, cognitive insight, self-esteem and treatment adherence. Regression models for repeated measures will be used for each proximal target, with the treatment group (P-MCT or classical MCT) included as a covariate for comparison. Additionally, mean differences between baseline and post-treatment scores in each group will be compared using Student’s t-tests, or Mann-Whitney tests if the assumption of normality is violated. Missing data will be handled using multiple imputation techniques. Subgroup analyses will be conducted based on sex, age, and baseline symptom severity. Sensitivity analyses will assess robustness of findings. ANCOVAs will explore whether responses differ across participant profiles (44), with treatment as the independent variable and composite participant profiles as a fixed factor. Covariates will include number of sessions attended, online vs. face-to-face delivery, and session frequency. Participant profiles will be identified using unsupervised ML techniques.

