#### Platform validation (H2)

2.7.2

In the classical MCT group, the predictive accuracy of the platform will be evaluated by comparing actual results with predictions in the five key variables (positive symptoms, delusions, insight, self-esteem, and treatment completion), with predictive performance assessed using the AUC for classification models (45) and RMSE and the R^2^ determination coefficient for regression models (46). In the P-MCT group, the analysis will focus on whether this approach led to improved outcomes compared to baseline predictions. Effect sizes will be calculated using Cohen’s d.

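### H1 has two efficacy tests per target and no statement of which one decides, and the change-score test leaves the baseline score unadjusted

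*Protocol article*

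**What the plan says.** The Comparative efficacy (H1) section sets out two analyses of the same outcomes.

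- **Regression.** A repeated-measures model is fitted to each target separately. The only statement on how treatment enters it is "with the treatment group (P-MCT or classical MCT) included as a covariate for comparison". The text names no treatment-by-visit term, baseline term or target visit, and it excludes none of these.
- **Change-score test.** As an addition, "mean differences between baseline and post-treatment scores in each group will be compared using" one of two tests: Student's t, or Mann-Whitney where normality does not hold. The phrase about each group is loose, but Mann-Whitney compares independent samples, so I read this as a between-arm comparison of changes.

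The section does not say which result settles H1. The covariates it lists are sessions attended, delivery format and session frequency. That list follows the sentence on exploratory ANCOVAs by participant profile, and the baseline score is not in it.

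The Data collection section has variables measured at baseline, post-treatment and six months, with listed exceptions. The Platform validation (H2) section evaluates predictions "in the five key variables (positive symptoms, delusions, insight, self-esteem, and treatment completion"), whereas the H1 section speaks of treatment adherence.

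**The concern.** Two tests of one hypothesis on the same data will sometimes disagree. Unless one is designated in advance, the favourable one can be reported as the answer. Nominal 5% error then holds for each test alone but not for the pair.

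The switch to Mann-Whitney adds a further choice made on the observed data. It also changes what is compared, from a difference in means to a rank comparison. With about 105 per arm, a comparison of means does not need that protection.

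The change score also gives away precision. Subtracting baseline fixes its coefficient at 1, whereas ANCOVA estimates the coefficient. In a randomised comparison ANCOVA has the smaller variance at any correlation below 1, and the data it needs are already collected.

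**Working it through.** **Inputs.** From the Sample size calculation section: "To achieve a two-tailed size effect" "of 0.5 with 95% power, using the total PANSS scores and balanced observations in the two groups"; "the estimated size is 210 in total". The article states neither α nor the within-patient correlation ρ. I assume α = 0.05 two-sided, ρ from 0.3 to 0.7, SD = 1 at every visit and equal correlation between visits. The planning effect was set for total PANSS; applying d = 0.5 to each target is also an assumption.

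**The plan's own figure.** Normal approximation: n per arm = 2(1.960 + 1.645)²/0.5² = 103.96, so 104 per arm and 208 in total. The exact two-sample t-test gives 104.93, so 105 per arm and 210 in total, as stated. I use 105 per arm below.

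**Precision of the change score.** The variance per patient is V = 2(1−ρ) for the change score and V = 1−ρ² for ANCOVA on the post-treatment score. The ratio is 2(1−ρ)/[(1−ρ)(1+ρ)] = 2/(1+ρ). Power = Φ(0.5/√(2V/105) − 1.96).

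Worked at ρ = 0.3:
- Change: V = 1.4, standard error √(2×1.4/105) = 0.163, 0.5/0.163 = 3.06, Φ(1.10) = 0.865.
- ANCOVA: V = 0.91, standard error 0.132, 0.5/0.132 = 3.80, Φ(1.84) = 0.967.

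| ρ | Variance ratio | Power, change | Power, ANCOVA | Total N for 95%, change | Total N for 95%, ANCOVA |
|---|---|---|---|---|---|
| 0.3 | 1.54 | 0.865 | 0.967 | 292 | 190 |
| 0.5 | 1.33 | 0.952 | 0.987 | 208 | 156 |
| 0.7 | 1.18 | 0.997 | 0.999 | 126 | 108 |

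The change score falls below the planned 95% power only when ρ is under about 0.5.

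**Two unranked tests.** These figures come from 20,000 simulated trials at each of ρ = 0.5 and ρ = 0.7, with no treatment effect, three visits and 105 per arm. Each single test rejected in about 5% of trials. The chance that at least one of two rejects was:
- 9.5% and 9.6% for the change t-test paired with a regression testing a treatment main effect over all three visits;
- 7.3% and 7.6% for the change t-test paired with a regression testing the mean of the two later visits minus baseline.

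With a true d = 0.5, the first pair disagreed on significance in 20% (ρ = 0.5) and 24% (ρ = 0.7) of trials. The second pair disagreed in 4.3% and 0.3%.

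**Regression, conditional case.** Suppose baseline is one of three outcome visits, treatment enters as a main effect with no treatment-by-visit term, and the true effect is 0.5 SD at both later visits. The estimate is then (0 + 0.5 + 0.5)/3 = 0.33 SD, with V = (1+2ρ)/3. At ρ = 0.5 the standard error is √(2×0.667/105) = 0.113, 0.333/0.113 = 2.96 and power is Φ(1.00) = 0.841. Power is 0.911 at ρ = 0.3 and 0.770 at ρ = 0.7. If baseline is not an outcome, or a treatment-by-visit contrast is tested, there is no dilution.

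**The case against.** The change-score comparison is valid in a randomised trial, and at ρ of 0.5 or more it meets the planned power. That stands: the loss is one of efficiency, not of validity.

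The t-tests are introduced as an addition, which suggests a supplementary role, and the trial is called an exploratory proof of concept. This softens the point but does not remove it. The Study design section says the trial is designed to assess superiority, the Introduction labels H1 primary, and no sentence ranks the two analyses.

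Two stronger readings are tempting.

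- **Dilution.** A reader might infer from the covariate wording that the regression estimates only half to two-thirds of the true effect. The article does not say that baseline is in the outcome vector or that a treatment-by-visit term is absent, and dilution needs both. The half figure also needs a two-visit model, although three assessments are planned. Full model terms may stand in an analysis plan that is not shown.
- **Adherence.** A reader might infer that neither analysis can be run on treatment adherence because completion has no baseline value. Completion is named only for platform validation. The H1 section says adherence, the Data collection section does not list adherence among the exceptions to three-visit measurement, and the instruments are in a supplementary table that is not shown. The two may be different measures.

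**Conclusion.** The concern holds in a limited form. The article states two efficacy analyses per target without naming the one that decides H1. Treating either as decisive would raise the false-positive rate to about 7% to 9.5% per target; the exact value depends on which regression contrast is tested.

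The change-score test needs 18% to 54% more patients than ANCOVA for the same power over ρ = 0.7 to 0.3. In power at 105 per arm, the loss is about 10 percentage points at ρ = 0.3, 3 to 4 at ρ = 0.5 and negligible at ρ = 0.7. These sizes rest on the assumed ρ, equal variances and α = 0.05.

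Dilution to 0.33 SD applies only under the conditions given with that calculation. It is a reason to state the model terms, not a demonstrated error.

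**What to change.** Name one primary analysis for each continuous target: a mixed model on the post-treatment and six-month scores, with baseline score as covariate and terms for visit, treatment and treatment-by-visit. Read the treatment contrast at post-treatment. This settles the deciding test, uses the baseline score and rules out dilution.

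Label the t-test or Mann-Whitney comparison supportive, or drop it. Say how treatment adherence is measured for H1. If it is completion, analyse it as a binary outcome, for example by logistic regression, because it has no baseline value.

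The cost is the rewording of a few sentences before the data are analysed. No new data are needed.

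At the planned 210 evaluable patients, ANCOVA on the post-treatment score would have power of 0.967, 0.987 and 0.999 at ρ = 0.3, 0.5 and 0.7, so the planned 95% would be met across that range.
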